## Methods

### Evaluation of the EscapeCovid Game

#### Mixed Methods Research Design

The EscapeCovid Game is evaluated through a mixed-methods approach using exclusively online data from a Randomized Controlled Trial (RCT) including 2 web-based questionnaires, and video interviewing. Within the mixed methods framework, we apply the embedded design [17]. According to this design, the quantitative and the qualitative data are collected simultaneously, but the qualitative data is embedded within the quantitative data. This means that the data from the questionnaires is prominent, but we still need to understand how the qualitative data further explains the effectiveness of the intervention.

As for the cocreation of the Escape Game, all tasks of the evaluation are conducted jointly by the university research team and the private start-up, thus proving the sharing of skills and the management of potential risks and their solutions in a combined effort. In particular, the research team is in charge of the collection and analyses of the data, while the start-up handles logistics including the organization of the game sessions. The postulate of the start-up is that a product can be really evaluated as significantly efficient in the serious game industry mostly or exclusively through the collaboration with a public research laboratory.

#### The Randomized Controlled Trial

We implement a rigorous RCT design using pre- and postintervention data coming from online self-administered questionnaires. The sample must be of at least 500 students at the University of Bordeaux. We estimated a sample size of 500 participants for the 2 arms: statistical power=.80, Cronbach α=.05, Cohen *d*=0.5, and 40% attrition with a 2:1 allocation ratio for the intervention group.

At study entry, the 500 students complete the online baseline questionnaire. Among them, 250 students play the EscapeCovid Game while 250 students receive an email with tips and resources for managing their stress during the COVID-19 pandemic. Participants are randomized so that the 2 groups are similar in terms of sex, age, and field of study (stratified balanced randomization). Participants are informed from the beginning of the study that they can be allocated to either the intervention of interest or the comparator. We tell students in the control arm that they are in a waiting list and that they can play the game once the experiment is concluded.

Inclusion is stopped when at least 500 participants have completed at least 3 quarters of each questionnaire, and 250 have played the game until the end. The statistician and the project manager of the EscapeCovid study are in charge of generating the random allocation sequence, enrolling participants, and assign them to one of the 2 arms.

Briefly, the 250 students of the intervention arm (1) complete the online baseline questionnaire, (2) play the EscapeCovid Game at their home within the week after the online baseline questionnaire—a link to the game is given at the end of the questionnaire, and (3) complete the same online questionnaire of the baseline plus some items on the appreciation of the game (satisfaction survey) 2 days after having played the game. After some tests with Tricky staff, the game duration is estimated at about 2 hours, from the online registration with the creation of an account, until the end of the debrief. Instructions to connect and play online are provided in an email sent by the start-up to the student of the intervention arm 2 days before the game session.

The 250 students of the control arm will (1) complete the baseline online questionnaire, (2) receive the same day an email with tips and resources to manage their stress during the COVID-19 pandemic, and (3) complete the same internet-based questionnaire of the baseline 2 days after having received the email with tips and resources.

Students can complete all steps of the evaluation from anywhere using a smartphone or a computer. However, they can play the game exclusively from home, considering the need for a stable internet connection and a performance computer.

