Finally, a maximum of 5 reminders will be sent through email to all 500 participants for the completion of the second questionnaire. For the intervention group, an additional maximum of 5 reminders will be sent to schedule a game session and eventually play the game. An additional maximum of 5 reminders will be sent to the students randomly selected to be interviewed. If after the 5 reminders per phase of the study, the student does not reply, we will proceed with the invitation of new students from the contacts we have from the University and attached associations.

The participation to the study is completely voluntary and all students are rewarded with a €20 (US $21.59) gift card.

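### By plan the control arm is retested 2 days after baseline and the game arm 2 to 9 days after, so time since baseline is confounded with arm

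*Protocol article*

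**What the plan says.** Both schedules are stated in full in the protocol article, Methods, The Randomized Controlled Trial.

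- **Control arm.** After the baseline questionnaire, students "receive the same day an email with tips and resources to manage their stress during the COVID-19 pandemic". They then "complete the same internet-based questionnaire of the baseline 2 days after having received the email with tips and resources".
- **Game arm.** Students "play the EscapeCovid Game at their home within the week after the online baseline questionnaire" and repeat the questionnaire "2 days after having played the game". The same section adds that the start-up emails connection instructions to these students 2 days ahead of the session.

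Recruitment of Study Population describes two sets of reminders. One applies to both arms: "a maximum of 5 reminders will be sent through email to all 500 participants for the completion of the second questionnaire". The other applies to one arm only: "For the intervention group, an additional maximum of 5 reminders will be sent to schedule a game session and eventually play the game". The spacing of the reminders is not given.

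Quantitative Data Analyses names an individual-level intention-to-treat linear regression of game against control as the primary analysis, adjusted for gender, age, field of study, year of study and self-perceived health. Elapsed time is not in that list, and nothing in the article brings the two intervals into line.

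**The concern.** The outcomes are self-reported, and the core questionnaire is the same on both occasions. A repeat after 2 days and a repeat after about a week differ in how well earlier answers are remembered and in how much mood, stress or workload may have changed. The literacy, beliefs and coping items are exposed mainly to recall. The depression, anxiety and stress scales are exposed mainly to ordinary change over time.

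Randomisation balances the students but not the calendar, because the interval is set by arm after allocation. Any change that depends on time since baseline therefore enters the estimated effect of the game. At stake is whether a modest arm difference can be credited to the game and not, in part, to a later retest.

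**Working it through.** **Inputs (protocol article, The Randomized Controlled Trial)**

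- Control: baseline to email, 0 days; email to post-test, 2 days.
- Game: baseline to session, 0 to 7 days; session to post-test, 2 days.
- Game: instructions are emailed 2 days before the session.
- Planned effect size: Cohen d = 0.5.

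The plan states no figure for the baseline-to-post-test interval, so there is none to reproduce.

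**Step 1. Interval by arm**

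Interval = (baseline to intervention) + (intervention to post-test).

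- Control: 0 + 2 = day 2.
- Game: (0 to 7) + 2 = day 2 to day 9.
- Game, if the instruction email can go out only after baseline: (2 to 7) + 2 = day 4 to day 9. The planned schedules of the two arms then do not overlap.

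**Step 2. Excess in the game arm**

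For a session on day g, the excess is (g + 2) − 2 = g days. Assuming sessions are spread evenly over whole days:

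- Sessions on days 0 to 7: (0 + 1 + ... + 7) / 8 = 28 / 8 = 3.5 days.
- Sessions on days 2 to 7: (2 + 3 + ... + 7) / 6 = 27 / 6 = 4.5 days.

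**Step 3. What that could mean for the arm difference**

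The documents give no rate of drift. As an assumption, take 0.05 to 0.15 SD per week, in either direction. Shift = weekly drift × mean excess / 7.

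| Mean excess | Drift 0.05 SD per week | Drift 0.15 SD per week |
|---|---|---|
| 3.5 days | 0.025 SD | 0.075 SD |
| 4.5 days | 0.032 SD | 0.096 SD |

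Relative to d = 0.5, the range is 0.025 / 0.5 = 5% to 0.096 / 0.5 = 19%.

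**Step 4. Can the analysis remove it?**

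Not cleanly. By plan the interval is constant in the control arm, so a covariate for it is almost a relabelling of arm. In the game arm it is settled after randomisation, by when the student manages to play. Adjusting for it would not restore a randomised comparison.

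**The case against.** The strongest defence is that both arms are measured 2 days after exposure. For a short-term gain in knowledge or skill that is a sensible anchor, and it may be deliberate. This stands as a reason to keep the 2-day rule. It does not answer the point, because time since baseline can be aligned without giving that rule up.

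The second defence is that real intervals will differ from planned ones in both arms. This also stands. Reminders for the second questionnaire go to everyone, so control post-tests can run late too. The game arm has an additional scheduling step with its own reminders, so slippage need not be equal, but the article does not allow its size to be worked out.

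Three stronger readings are tempting and are not supported:

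- **That the game-arm interval is open-ended.** A reader might infer this from the scheduling reminders. They are capped at 5, after which new students are invited, and their spacing is not stated.
- **That the bias reaches 10 to 30% of the planned effect.** That follows from the same assumed drift only if every game student plays on day 7.
- **That regression to the mean in distressed enrollees inflates the benefit of the game.** The inclusion criteria set no symptom threshold, and nothing says that students join when distressed. The direction could equally be the reverse: control students retested after 2 days may remember the items better, which could raise their literacy scores and make the comparison conservative.

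**Conclusion.** The point holds as a matter of design. By plan, time since baseline is 2 days in the control arm and 2 to 9 days in the game arm (4 to 9 if the instruction email must follow baseline), and the primary analysis cannot separate elapsed time from treatment. The intervals come directly from the article.

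The size and direction of any bias do not. The range of roughly 0.03 to 0.10 SD rests on two assumptions: an even spread of sessions over the week and a drift of 0.05 to 0.15 SD per week. It treats all outcomes alike, although recall and mood change would act differently on different scales. At that size the problem would not by itself explain an effect as large as d = 0.5, but it could matter for a smaller one. It should be corrected because correction is cheap, not because a large bias has been shown.

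**What to change.** **For students still to be enrolled**

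- Send the control email on days that follow the distribution of game-session dates within the planned week, and keep the post-test 2 days later in both arms. This preserves the match on time since exposure and removes the planned gap in time since baseline. The required sample size is unaffected.
- Give randomised students who do not play a post-test at the end of the one-week window plus 2 days, that is day 9. The stated game-arm post-test is tied to having played, and the Study Population section under Results reports that 23 of 90 game-arm students had played by 4 November 2024. An intention-to-treat analysis needs a defined time point for the others as well.

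**For all students**

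- Record the baseline, session or email, and post-test dates, and report the baseline-to-post-test interval by arm.
- Show results separately for those enrolled before and after the change.
- Do not rely on the interval as a covariate to repair the comparison for those already enrolled.

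**Cost.** The change is mainly one of email scheduling. Control follow-up becomes up to a week longer and may lose a few more replies, which matters in a trial that already finds retention hard. Two control schedules will exist within one trial, which is why the before-and-after results should be shown. At the last report 191 of the planned 500 students had completed baseline, so 309 were still to come and the change could cover most of the sample.

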#### Internet-Based Interviews

There are two sources of qualitative data: (1) semistructured interviews after the intervention with students from both arms and (2) open discussion with the game guide at the end of the game session. Concerning the first source of qualitative data, 20 students were randomly selected among the 2 groups (10 for the intervention arm, and 10 for the control arm) to respond to a semistructured interview. For the discussion embedded in the game, the text produced during the debrief is recorded and analyzed so that the developers of the start-up can work on an algorithm for building a chatbot messenger capable of providing tailored advice to gamers, replacing the game guide. Machine learning will be used for this purpose. In terms of simplicity and feasibility, the sample is recruited on the sole criterion of sex, 50% of girls, through sample saturation. The interviews have been conducted remotely by a public health researcher through an internet-based interview tool. Students are recommended to make the interview at home.

#### Recruitment of Study Population

Inclusion criteria are (1) being a student at the University of Bordeaux, (2) being aged ≥18 years, (3) understanding, speaking, and writing French, and (4) having given the electronic consent to be enrolled in the study. We consider that students have a sufficient level of computer literacy for playing the game as only few basic skills are required: knowing how to navigate the web, keyboarding, and typing. These skills are essential for any student from any field of study and represent a prerequisite for the undergraduate and graduate programs at the University of Bordeaux.

Students are invited through the social media of the study partners (University of Bordeaux and Tricky), posts in the Facebook groups of more than 100 student associations, and mailing lists from the University of Bordeaux. The associations are manually selected from a list provided by the University of Bordeaux to cover the different fields of study. Overall, we plan to reach about 10,000 students which is a substantial number considering potential very low enrollment and retention rates. The invitations by email are sent to a maximum of 500 recipients at a time, so that we can proceed step by step with the inclusion of participants and the organization and schedule of the game sessions. The invitations will be sent until we reach a sample of a minimum number of 500 students.

The recruitment is exclusively web-based. Clicking on the link displayed on social media posts or on the text of the email, students will access an online form to enter the study.

The inclusion of participants to the RCT will be conducted based on a continuous monitoring through statistical analysis. Data on sex are available only for males and females, since information on gender is not reported in the University records. The year of study goes from 1 (first year of university) to >8 (corresponding to a doctoral degree or a diploma in medicine). The fields of study offered by the University of Bordeaux are more than 50,000 and are categorized in Health Studies, Law and Economics, Technical Sciences, and Human and Social Sciences.

Finally, a maximum of 5 reminders will be sent through email to all 500 participants for the completion of the second questionnaire. For the intervention group, an additional maximum of 5 reminders will be sent to schedule a game session and eventually play the game. An additional maximum of 5 reminders will be sent to the students randomly selected to be interviewed. If after the 5 reminders per phase of the study, the student does not reply, we will proceed with the invitation of new students from the contacts we have from the University and attached associations.

The participation to the study is completely voluntary and all students are rewarded with a €20 (US $21.59) gift card.

#### Data Collection Tools

The pre and postintervention questionnaires are administered through the Sphinx software (Georg Brandl) distributing surveys on all media (web, smartphone, QR code, and SMS). The data are automatically imported in a Microsoft Excel file.

The first questionnaire is composed of 112 items. It includes validated scales measuring mental health literacy (French Mental Health Literacy Scale [MHLS-FR]) [18], beliefs about mental health (Health Belief Model [HBM]) [19], emotions (Plutchik’s wheel of emotions) [20], Coping Strategies (Ways of coping questionnaire) [21], Depression (Patient Health Questionnaire-9 [PHQ-9]) [22], Anxiety (Generalized Anxiety Disorder-7 Scale [GAD-7]) [23], Stress (Perceived Stress Scale [PSS4]) [24], and Help-seeking actions (Kessler Psychological Distress Scale in help-seeking youth [K6]) [25]. Sociodemographic information (email address, gender, date of birth, field of study, year of study, and self-perceived health) are also collected to assess the representativeness of the sample (stratifications by sex, age, field of study etc). A question specifically asks the gender giving students the possibility to indicate whether they belong to the LGBT (lesbian, gay, bisexual, and transgender) category (considering the confidentiality of this data). The question of gender as a determinant of mental health will be important to analyze the results considering this confounding variable if the number of individuals is sufficient. The questionnaire is developed by several researchers through different stages of drafts and reviews, following a structured survey construction method in 5 steps [26]. Operational staff members from the team of the coordinator and a group of students pretest the questionnaire for readability, comprehensibility, and face validity. The response modalities are varied: multiple choice, binary responses, Likert scales, and visual analog scales. Mental health indicators and appreciation and relevance results are the main outcomes of the study. All items provided the nonresponse option “not applicable,” “I don’t know,” and “I do not want to answer.” Respondents are required to select an option from a predefined list. The questionnaire is not validated if at least one question is not answered. Respondents are not able to review and change their answers, but they can ask the principal investigator for a document with exclusively their answers. Corrections cannot be made manually in the database in order to avoid any further error.

The second questionnaire is the same, but it does not include the sociodemographic items. It contains new items on the appreciation and relevance of either the game or the email (satisfaction survey). These items are created ad hoc, but are also inspired by existing instruments evaluating digital health interventions (eg, items by Fadda et al [27]). The questionnaires, composed of both validated scales, sociodemographic items, and satisfaction survey questions, have been developed by 1 researcher and 1 project manager in public health. A pool of researchers in psychology and in statistics have reviewed the questionnaire to assess its readability, understanding, and relevance. The questionnaires have been tested on the internet by 10 students of the School of Public Health of the University of Bordeaux. Testers reported some technical errors, that has bugs and repetitions of items, and suggested different wording for making the questionnaires more adapted to a young target population between 18 and 25 years of age. The questionnaires were constructed following the CHERRIES (Checklist for Reporting Results of Internet E-Surveys) [28]. For both questionnaires, outcomes are self-assessed. The questionnaires are available in Multimedia Appendix 1.

Qualitative data from the semistructured interviews are collected through an ad hoc grid including questions on the impact of the game or email on mental health–related knowledge, on the access to mental health care services and the attitudes toward mental illnesses or stigmatization. Participants are particularly asked to evaluate whether the game is adapted to their needs and to discuss the cocreation approach as a means to produce tailored interventions. The main objective of these interviews is to assess the appreciation and the relevance of the game. The interview grids are available in Multimedia Appendix 2.

Questions addressed to the control group allow to capture the utility of the contents of the email (eg, list of mental health care services and a short description of mental health problems) and to compare the contribution of each tool to knowledge about mental health. Qualitative data form the debrief correspond to the free discussion between the players and the game guide. The latter follows a script and makes questions on the specific topics covered by the game: overall recognition and management of the emotions; symptoms of depression, stress and anxiety; relevance of mental health in daily life; and sources available in the case of a mental health problem.

The semistructured interviews were conducted by a public health researcher trained in qualitative data analyses. The project manager analyzed the same dataset using the triangulation approach.

The quality of both quantitative and qualitative data is ensured by keeping documentation accurate, that are clean databases and well-stored texts. Ensuring ethical standards is a further guarantee of the quality of this study.

### Data Analyses

#### Overall Mixed Methods Analyses

First, we will conduct statistical analyses on quantitative data (descriptive statistics, modeling, and exploratory data analysis) processed from the RCT; second, we have analyzed the discourse of qualitative data (thematic analysis based on a predefined interview guide); and third, we will couple the analysis of both types of data. In particular, we will integrate quantitative and qualitative data for the purposes of convergence, contextualization, and expansion to gain a detailed understanding of the evaluation and impact of the game.

#### Quantitative Data Analyses

For the data from the RCT, we will compare the answers between exposed and nonexposed students (intergroup) and measure the change in their answers within the intervention group before and after playing the game and debriefing (intragroup). Our primary analysis will be based on intention-to-treat at the individual level using linear regression comparing the outcomes of the intervention and the control arm. We will measure our primary outcomes in terms of absolute scores and as a percentage of the total possible score. We will control baseline covariates: (1) gender, (2) age, (3) field of study, (4) year of study, and (5) self-perceived health. We will analyze the data from all participants only if at least 3 quarters of the questions are completed. We consider that some users will not go through all questionnaire pages. Missing values will be imputed by replacing them with the mean or median values of the dataset at large, or some similar summary statistics.

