### The EscapeCovid Game

The EscapeCovid Game is focused on four main outcomes: (1) mental health literacy (knowledge of the concept of mental health, from illnesses to psychological well-being), (2) appraisal and change of beliefs about mental health (destigmatization), (3) management of emotions (their recognition and regulation), and (4) development of coping strategies (building resilience). It addresses specifically anxiety and depression whose symptoms were exacerbated by the COVID-19 crisis including the measures undertaken to limit the spread of the virus (eg, repeated lockdowns and curfews, University closure).

The underpinning theories of the game are the COM-B model of behavior (capability, opportunity, and motivation to change behavior) [12], the Plutchik’s wheel of emotions (visualization of emotions to change behavior) [13], and the Transtheoretical model of behavior change (stages of change, processes of change, levels of change, self-efficacy, and decisional balance [14]).

The EscapeCovid Game takes place in Thomas’ apartment which he shares with another student, Hana. Thomas is a university student and we follow him during a typical day in lockdown. To move from one room to another, players must solve all the puzzles by clicking on the objects spread out in Thomas’ room. At the end of each room scenario, a set of cards is shown, with each card containing a mental health-related message. The cards synthesize the messages transmitted through the puzzles in the room.

The game can be played in groups of 4 players who help each other and discuss using their computer cameras and headphones. All along the game, they are helped by a game guide who explains the rules and answers any questions. The same guide concludes the game session with a final debrief where all participants share their experiences.

The EscapeCovid Game has been cocreated jointly by a team of researchers at the University of Bordeaux and a start-up specialized in the production of both physical and digital Escape Rooms, Tricky, in France. We used the PRODUCES (Problem, Objective, Design, End Users, Cocreators, Evaluation, and Scalability) framework [15] composed of 3 steps. First, we tested the hypothesis that the game was effective in promoting the four mental health-related outcomes. Second, we accumulated evidence on the good functioning of the game. Third, we leveraged the right behavior change mechanisms.

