### Objective and Hypotheses

The objective of this study is to evaluate among a population of university students the effectiveness of the EscapeCOVID Game on 4 mental health outcomes: mental health literacy, appraisal and change of beliefs about mental health, management of emotions, and development of coping strategies. The appreciation and relevance of the game are also considered in the overall evaluation of the game. This stand-alone intervention is implemented in the era of the COVID-19 pandemic.

Consequential research hypotheses of the study are (1) compared with a group receiving another classical intervention, after playing the digital Escape Game and having received a debriefing, students remarkably improve their mental health literacy, appraisal, and change of beliefs about mental health, management of emotions, and development of coping strategies; and (2) cocreation enhances appreciation and relevance of the digital Escape Game among university students.

The objective of this study is original since, to the best of our knowledge, no Escape Game on students’ mental health outcomes has been developed before following a cocreation approach and evaluated through mixed-methods to prove its effectiveness.

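### The game is delivered in shared sessions but the primary regression makes no allowance for session, so its standard errors are too small if outcomes within a session are positively correlated

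*Protocol article*

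**What the plan says.** Allocation is by student: "Participants are randomized so that the 2 groups are similar in terms of sex, age, and field of study" (protocol article, The Randomized Controlled Trial).

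Delivery differs between the arms. For the game, "The game can be played in groups of 4 players who help each other and discuss using their computer cameras and headphones", and "The same guide concludes the game session with a final debrief where all participants share their experiences" (The EscapeCovid Game). The first hypothesis makes the debrief part of what is tested, since improvement is expected "after playing the digital Escape Game and having received a debriefing" (Objective and Hypotheses). Control students "receive the same day an email with tips and resources to manage their stress during the COVID-19 pandemic" (The Randomized Controlled Trial), with no group element.

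Under Quantitative Data Analyses the primary analysis is "intention-to-treat at the individual level using linear regression comparing the outcomes of the intervention and the control arm". Its adjustment set is listed: "We will control baseline covariates: (1) gender, (2) age, (3) field of study, (4) year of study, and (5) self-perceived health". The same section plans a before-after comparison within the game arm alone. No session or guide term, clustered standard error, ICC or design effect appears there or among the sample-size inputs.

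**The concern.** Four students who solve the same puzzles together and share one debrief may answer the follow-up questionnaire more alike than four unconnected students. Control students have no such link. Linear regression with its usual standard errors treats every student as an independent observation. With positive correlation within sessions, the game-arm mean is less precise than the model assumes. Intervals for the arm difference are then too narrow, and a nominal 5% test rejects too often under the null.

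This matters because the article says, under Future Directions, that a positive result will lead to commercialisation of the game to universities. The within-arm before-after comparison is more exposed, because no unclustered control arm dilutes the effect.

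**Working it through.** **Inputs from the protocol article**
- Session size m = 4 (The EscapeCovid Game; worded as a possibility).
- Total 500, described as 250 and 250; d = 0.5; 40% attrition; "statistical power=.80, Cronbach α=.05" (The Randomized Controlled Trial). I read the 0.05 as a two-sided significance level.
- 23 students had played out of 90 allocated to the game by November 4, 2024 (Study Population).

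**Assumed, not in the article**
- ICC from 0.01 to 0.20, for outcomes after covariate adjustment.
- Equal total variance in the two arms.

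**1. The stated sample size.** Control-arm n = (1 + 1/k) × (1.96 + 0.8416)² / 0.5², where k is the game-to-control ratio.
- At 2:1: 1.5 × 7.849 / 0.25 = 47.1, so 48 + 96 = 144, and 144 / 0.6 = 240.
- At 1:1: 2 × 7.849 / 0.25 = 62.8, so 63 + 63 = 126, and 126 / 0.6 = 210.

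The 500 is not reproduced, and the stated 2:1 ratio conflicts with 250 and 250. Nothing below depends on either.

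**2. Between-arm comparison, all analysed game-arm students having played in full sessions.**
- Game-arm design effect: DE = 1 + (m − 1) × ICC = 1 + 3 × ICC.
- With equal arms, true SE / model SE = R = √[(1 + DE) / 2].
- Real type I error = 2 × [1 − Φ(1.96 / R)].

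| ICC | DE | R | Type I error |
|---|---|---|---|
| 0.01 | 1.03 | 1.007 | 5.2% |
| 0.05 | 1.15 | 1.037 | 5.9% |
| 0.10 | 1.30 | 1.072 | 6.8% |
| 0.20 | 1.60 | 1.140 | 8.6% |

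At ICC 0 there is no bias. Simulation (20,000 trials per setting, 148 per arm, t test) gave 4.8, 5.9, 6.7 and 8.3% at ICC 0, 0.05, 0.10 and 0.20, in line with the formula. The number of students cancels out of R, so reaching 500 does not remove the inflation. At 2:1 allocation the figures are 5.1, 5.6, 6.2 and 7.4%.

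**3. Smaller sessions.** At ICC 0.10, with m the number of analysed players per session:
- m = 3: R = √[(1 + 1.20) / 2] = 1.049, type I error 6.2%.
- m = 2: R = √[(1 + 1.10) / 2] = 1.025, type I error 5.6%.

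**4. Non-players kept under intention-to-treat.** If a fraction f of the analysed arm played, the arm's average design effect is 1 + 3 × ICC × f. With f = 23/90 = 0.256 and ICC 0.10, it is 1.077, R = √[(1 + 1.077) / 2] = 1.019, and the type I error is 5.4%. At ICC 0.01, 0.05 and 0.20 it is 5.0, 5.2 and 5.9%. With f = 0.8 and ICC 0.10 it is 6.4%.

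**5. Before-after comparison within the game arm.** Here R = √DE. If change scores have the same ICCs and all players sat in full sessions, R = 1.015, 1.072, 1.140 and 1.265, and a nominal 5% test has a real level of 5.3, 6.8, 8.6 and 12.1%.

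**6. Power.** With 500 enrolled and 40% lost, 150 per arm remain.
- No clustering: SE = √(2 / 150) = 0.1155; Φ(0.5 / 0.1155 − 1.96) = 99.1%.
- ICC 0.20: SE = √(2.6 / 150) = 0.1317; Φ(0.5 / 0.1317 − 1.96) = 96.7%.

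Allowing for clustering at ICC 0.20 and 40% attrition, the total needed for 80% power is 274 (1:1) or 285 (2:1), well under 500.

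**The case against.** The strongest reply is that a condensed article gives the population, unit and model family and leaves the variance estimator to an analysis plan that is not shown. Clustered standard errors would be compatible with the quoted sentence. This stands in part: the article does not rule them out. But it specifies the level of analysis, the model and a closed list of covariates, and nothing in it points to an allowance for session. As stated, the method does not match the delivery the same article describes.

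Three further limits stand in full. Groups of four are described as possible, not required, and the trial procedure fixes no session size. The outcomes are individual self-report scales taken two days after a single session of about two hours, so the ICC may be low. Students who never play add no session correlation, and the interim uptake was 23 of 90. That count is only a snapshot: inclusion is meant to continue until 250 students have finished the game, so final uptake is unknown.

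A reader might infer more than the article supports:
- **That the type I error is certainly above 5%.** It is so only if the ICC is positive, and no ICC is given.
- **That the missing design effect leaves the trial underpowered.** Step 6 shows that it does not at d = 0.5.
- **That guide effects must add to the problem.** The number of guides is not stated, and the debrief follows a script.
- **That team support is the declared mechanism of this game.** The Introduction offers it as an example of what Escape Games in general can do.

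**Conclusion.** The point holds in conditional form. The design is partially nested, and the primary analysis as written ignores it. For an assumed ICC of 0.01 to 0.20, full sessions of four, equal arms and complete uptake, the correct standard error of the arm difference is about 1 to 14% larger than the model's. A 95% interval then covers about 94.8 to 91.4% of the time. With partial uptake or smaller sessions the effect shrinks, and at the interim uptake it is slight. The within-arm before-after test carries the full design effect and is the more exposed of the two. The consequence is for precision and false-positive risk. Power at d = 0.5 with 500 enrolled is secure, and no change to the sample size follows from this point.

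**What to change.** Record a session identifier for every player, and a guide identifier if more than one guide is used. Keep the intention-to-treat regression and its covariates, but state that standard errors are cluster-robust by session with a small-sample correction, each control student and each non-player forming a cluster of one. A mixed model with a random session intercept in the game arm only serves the same purpose. Apply the same allowance to the before-after comparison within the game arm. Report the estimated ICC and the distribution of analysed session sizes.

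The cost is one or two added data fields, a sentence in the analysis plan and slightly wider intervals. The start-up organises the sessions and emails players beforehand, so session membership should be recoverable for those who have already played. The article does not say whether guide identity is kept. If the ICC proves close to zero, the results will barely change.
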